### Costs and patient reported quality of life measures

Direct medical costs include both the immediate medical costs such as diagnostic tests and initial treatments (including side-effects), as well as later treatments. Direct costs incorporated in the current study include costs of standard diagnostic staging (CT+/−laparoscopy), CRS-HIPEC and treatment of recurrences, follow-up visits and palliative care. Resource use data will be collected from the hospital’s administrative database. Where appropriate, Dutch guidelines for costing studies will be used in applying tariffs to units of resource use [22].

For the health related quality of life (QoL), the EORTC-C30 questionnaire will be used [23]. For cost-effectiveness purposes, utilities will be measured, in order to derive quality-adjusted-life-years (QALYs). The utilities will reflect the preferences of society for length of life versus quality of life. The utilities will be derived from the trial by means of the EQ5D5L questionnaire [24]. The questionnaires are given to patients at baseline (T0), 3 months after the diagnostic staging and treatment (T1), and after 6 months (T2).

### Statistical analysis

#### Sample size calculation

Power calculations are based on an expected reduction of futile surgical explorations from 30 to 15% by MRI staging. With a two-sample two-sided test of binomial proportions and an α of 0.05, a ß of 0.20, and an expected drop-out rate of 20%, 272 patients are to be included in total.

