### Patient recruitment and randomization

Eligible patients are identified and informed about the study by their treating physician at the participating center. Patients are included after written informed consent. Patients are randomly assigned to an experimental arm (A) or a control arm (B). The random assignment is performed by dedicated medical data managers or a research nurse using specific clinical trial management software (ALEA clinical, Abcoude, The Netherlands). A random block randomization is used and stratified per participating center. Blinding is not possible with this trial set-up.

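### The total of 272 does not follow from the stated inputs: with the planned 20% drop-out it gives about 76–77% power, not 80%

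*Protocol article*

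**What the plan says.** The whole justification of the trial's size is in the protocol article, under Sample size calculation. The effect is given as "Power calculations are based on an expected reduction of futile surgical explorations from 30 to 15% by MRI staging". The test is a "two-sample two-sided test of binomial proportions", with "an α of 0.05" and a β of 0.20, so the claimed power is 80%. The section closes with the drop-out allowance and the total: "and an expected drop-out rate of 20%, 272 patients are to be included in total".

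Because 272 is the number to be included, it is the figure after the drop-out allowance. Neither the sample size formula nor the allocation ratio is given. Under Patient recruitment and randomization the article says only "A random block randomization is used and stratified per participating center".

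**The concern.** Every input that a standard two-proportion calculation needs is printed, apart from the allocation ratio, so the total can be checked without a fuller protocol or an analysis plan. It comes out too small for the stated power and drop-out together.

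This calculation supports the primary outcome. If the trial is neutral, readers will judge the result against 80% power after 20% loss. On the plan's own assumptions, the chance of missing a true halving of futile explorations would be about 23–24% with an uncorrected test, not 20%.

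**Working it through.** **Inputs** (Sample size calculation): p1 = 0.30, p2 = 0.15, two-sided α = 0.05 (z = 1.960), power 0.80 (z = 0.842), drop-out 20%, total 272. **Assumption:** 1:1 allocation, so 136 per arm. Unequal allocation would lower the power further.

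**Step 1. Evaluable patients needed per arm.** The mean proportion is (0.30 + 0.15)/2 = 0.225 and the difference is 0.15.

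- Pooled: n = [1.960·√(2·0.225·0.775) + 0.842·√(0.30·0.70 + 0.15·0.85)]² / 0.15² = 120.5, so 121.
- Unpooled: n = (1.960 + 0.842)²·(0.21 + 0.1275) / 0.0225 = 117.7, so 118.
- Arcsine: n = 2·[(1.960 + 0.842)/h]², with h = 2·asin√0.30 − 2·asin√0.15, = 118.6, so 119.
- Continuity-corrected: n' = (n/4)·[1 + √(1 + 4/(n·0.15))]² with the pooled n = 120.5, = 133.5, so 134.

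**Step 2. Allow for 20% drop-out and try to reproduce 272.** The correct inflation divides by 0.80. Multiplying by 1.20 is a common slip and is shown for completeness.

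| Formula | Evaluable total | ÷ 0.80 | × 1.20 |
|---|---|---|---|
| Pooled | 242 | 303 | 291 |
| Unpooled | 236 | 295 | 284 |
| Arcsine | 238 | 298 | 286 |
| Continuity-corrected | 268 | 335 | 322 |

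No two-sided variant gives 272. By the pooled formula with correct inflation the gap is 303 − 272 = 31 patients.

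**Step 3. Power that 272 delivers after 20% loss.** 272 × 0.80 = 217.6 evaluable, or 108–109 per arm.

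- Pooled: Φ{[0.15 − 1.960·√(2·0.225·0.775/n)] / √(0.3375/n)} = 75.5% (n = 108) to 75.9% (n = 109).
- Unpooled: Φ{0.15/√(0.3375/n) − 1.960} = 76.5% to 76.9%.
- Arcsine: 76.2% to 76.6%.
- Exact enumeration of the uncorrected chi-squared test: 76.4% to 76.9%.
- Exact enumeration with continuity correction, or Fisher's exact test: 70.6% to 71.2%.

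**Step 4. Drop-out at which 272 still gives 80%.**

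- Pooled: 1 − 242/272 = 30/272 = 11.0%.
- Unpooled: 1 − 236/272 = 36/272 = 13.2%.

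**Step 5. Routes that do land on or near 272.** Each contradicts a printed input.

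- One-sided α 0.05 with continuity correction: 108 per arm, 216/0.80 = 270. The article says two-sided.
- Two-sided with continuity correction and no drop-out allowance: 268. The article says 20% is allowed for.
- Unpooled with a 15% allowance applied by multiplication: 118 × 1.15 = 135.7, so 136 per arm and 272 in total. The article says 20%.
- Pooled with 11% drop-out: 242/0.89 = 271.9, so 272. Again not 20%.

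**The case against.** The strongest reply is that the gap is small. It is 3 to 4 points of power for an uncorrected test, and it appears only if the full 20% are lost. The 30% and 15% are themselves expectations, and the Discussion accepts that laparoscopy and open-close rates may differ between hospitals. A different control rate could move power by as much. All of this stands and limits the weight of the point. It does not make 272 follow from the inputs.

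A second reply is that the near matches suggest a misprinted input in a condensed article, not an undersized trial. That also stands: the document cannot show whether the total or one of the inputs is wrong. Either way the section needs correcting.

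A reader might go further and infer that the shortfall is harmless, because surgery is known for nearly every randomised patient, all 272 can be analysed, and power is then about 85% (84.6% pooled at 136 per arm). The document does not support this. Its own plan expects 20% loss. The endpoint under Outcome measures also depends on a PCI category (above 24 or below 15), so knowing whether surgery took place is not enough. The 85% further assumes that patients otherwise lost show the full 30% versus 15% contrast. If instead that 20% were counted as non-events in both arms, the rates would be 0.8 × 30% = 24% and 0.8 × 15% = 12%. The pooled formula at 136 per arm would then give Φ{[0.12 − 1.960·√(2·0.18·0.82/136)] / √((0.24·0.76 + 0.12·0.88)/136)} = about 73%.

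A reader might also infer the opposite: that the design cannot reach 80% power or must recruit more. That is too strong, since 80% is kept with losses up to about 11–13%.

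**Conclusion.** The point holds as an arithmetic inconsistency of modest size. The stated inputs call for 303 enrolled (pooled) or 295 (unpooled), not 272. With 272 enrolled and 20% lost, power is about 76–77% for the uncorrected two-sample test and about 71% with continuity correction.

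This rests on 1:1 allocation, on the 30% and 15% being true, and on the full 20% being lost equally in both arms. It concerns only the test named under Sample size calculation. Data analysis names a McNemar test for the comparison between arms, which is a separate question, and none of these power figures describe that test. The design, the endpoint and the number of patients are not called into question here.

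**What to change.** Reconcile the figure with its inputs under Sample size calculation. If the printed inputs are the intended ones, say that 272 randomised patients give about 76% power with 20% drop-out, and that 80% is reached only if no more than about 11% (pooled formula) to 13% (unpooled formula) are non-evaluable. Name the formula used, whether it is continuity-corrected, and the allocation ratio. If 272 was derived with a different sidedness or drop-out rate, correct that input instead.

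The cost is a change of text. No extra patients are needed. The price is a stated power a few points lower, or a tighter stated limit on losses.

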### Data analysis

The observed difference in preventable surgical explorations between trial arms will be tested with a McNemar’s chi-squared test, as well as the difference in incomplete CRS-HIPECs, non-peritoneal findings before surgery, and early recurrences or residual disease visible at first follow-up (6 months). Progression free survival will be analyzed by binomial logical regression analysis. Progression free survival is defined as the time in days from complete CRS-HIPEC to recurrence or progression of disease as determined by the multidisciplinary team meeting or death of any cause. Correlations between MRI staging and surgical staging will be evaluated by intraclass correlation coefficients (ICC), Cohen’s kappa, and Cohen’s weighted kappa, where appropriate. Diagnostic performance of MRI and surgical staging to predict complete CRS will be compared by confusion matrix analysis and receiver operator characteristic analysis. Differences in predictive values will be tested with McNemar’s test and the DeLong test, where appropriate.

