## Methods/design

This investigator-initiated, multi-center, randomized controlled trial is performed in Dutch HIPEC centers since September 2019. The study is conducted according to the principles of the Declaration of Helsinki and in accordance with the Medical Research Involving Human Subjects Act (WMO) and was approved by the medical ethics committee at the Netherlands Cancer Institute (date: 13-09-2019; ref. no.: NL70045.031.19) and is retrospectively registered in the clinical trials registry of U.S. National Library of Medicine under NCT04231175 (https://clinicaltrials.gov/ct2/show/NCT04231175). Patients suspected of having CRC peritoneal metastases and considered for CRS-HIPEC, are eligible for inclusion. Patients are randomly assigned to one of two diagnostic arms towards CRS-HIPEC. A trial flow diagram is presented in Fig. 1.

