### Outcome measures

The primary outcome measure is a composite endpoint of futile surgical explorations. A futile surgical exploration is defined as: all surgeries in patients with definitely inoperable disease (PCI > 24) or explorative surgeries in patients with limited disease (PCI < 15).

The secondary outcomes include:
number of incomplete CRS-HIPECs (R2a/ R2b/ open-close),number of residual disease events or early recurrences at 6 months after a complete resection at CRS-HIPEC,number of non-peritoneal metastases,diagnostic performance of MRI and diagnostic laparoscopy to predict whether complete CRS-HIPEC is feasible,correlations between MRI findings and surgical findings,incremental cost-effectiveness,Patient reported QOL between study arms.

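### The primary comparison of two independently randomised arms is to be tested with McNemar's test, which needs paired data, so the primary p-value would be invalid or arbitrary

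*Protocol article*

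**What the plan says.** Design: the Methods/design section states "Patients are randomly assigned to one of two diagnostic arms towards CRS-HIPEC". The Patient recruitment and randomization section adds "A random block randomization is used and stratified per participating center". Neither describes matching, pairing or crossover.

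Primary outcome: the Outcome measures section states "The primary outcome measure is a composite endpoint of futile surgical explorations", defined by the type of surgery and the PCI category. It is a yes/no result for each patient.

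Sample size: this section assumes an "expected reduction of futile surgical explorations from 30 to 15% by MRI staging", evaluated by a "two-sample two-sided test of binomial proportions".

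Analysis: the Data analysis section states "The observed difference in preventable surgical explorations between trial arms will be tested with a McNemar" (McNemar's chi-squared test). The same sentence extends the test to incomplete CRS-HIPEC procedures, non-peritoneal findings before surgery, and early recurrence or residual disease at six months. A later sentence in that section uses McNemar again for differences in predictive values. That is a different comparison and is not at issue here.

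**The concern.** McNemar's test takes two binary results on the same patient, or on matched patients, and compares the two kinds of discordant pair. In this trial a patient has one result in one arm. Blocked randomisation within centres balances numbers but creates no pairs. An analyst following the text would have two options: feed the arm-by-outcome table to a McNemar routine, or invent pairs across arms. The first tests the wrong hypothesis. The second makes the answer depend on which unrelated patients are put together.

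Some of the secondary outcomes make pairing harder still. Early recurrence is counted only after a complete resection, so the two arms need not contribute equal numbers and one-to-one pairing may not even be possible.

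The powered test and the analysis test also belong to different data structures, so the article contradicts itself on its primary analysis.

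**Working it through.** **Inputs.** The sample size section gives 272 patients, 20% drop-out, and event rates of 30% and 15%. The allocation ratio is not stated, so I assume 1:1. Evaluable patients per arm: 272 × 0.8 / 2 = 108.8, taken as 109. I take the preventable explorations of the analysis section to be the futile explorations of the outcome section. No continuity correction is used unless stated.

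**Reading 1: McNemar on the arm-by-outcome table.** Let A and B be the numbers of events in the two arms, each of size n. The off-diagonal cells are n − A (non-events in one arm) and B (events in the other). The statistic is

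(n − A − B)² / (n − A + B).

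It is zero when A + B = n, that is, when the pooled event rate is 50%. It does not measure the difference between arms.

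- Identical arms, 33/109 and 33/109: (76 − 33)² / (76 + 33) = 1849/109 = 16.96, p = 0.00004.
- 200,000 simulated null trials, 30% in both arms: rejection in 99.96%, against a nominal 5%.
- The same simulation with 50% in both arms: rejection in 0.6%. The result follows the pooled rate and not the treatment effect.

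**Reading 2: McNemar on invented pairs.** With x₁ and x₂ events and k pairs in which both members have the event, the discordant counts are x₁ − k and x₂ − k. The statistic is

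(x₁ − x₂)² / (x₁ + x₂ − 2k).

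The arm totals are fixed. Only k changes, and k is set by the pairing.

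Example, 31/109 versus 18/109. Pearson: pooled rate 49/218 = 0.2248; χ² = (13/109)² / (0.2248 × 0.7752 × 2/109) = 4.45, p = 0.035. McNemar: 13² / (49 − 2k).

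| Pairs with both events (k) | Statistic | p |
|---|---|---|
| 0 | 169/49 = 3.45 | 0.063 |
| 2 | 169/45 = 3.76 | 0.053 |
| 3 | 169/43 = 3.93 | 0.047 |
| 13 | 169/23 = 7.35 | 0.007 |
| 18 (maximum) | 169/13 = 13.0 | 0.0003 |

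Over 20,000 random re-pairings, p ran from 0.0067 to 0.0633 and was below 0.05 in 94% of them. With a continuity correction the numerator becomes 12² = 144, k must be at least 6 for significance (144/37 = 3.89), and only about 40% of random pairings reach it.

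For 30/109 versus 19/109, Pearson p is 0.074, while McNemar p can lie anywhere from 0.116 to 0.0009.

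**Operating characteristics under random pairing.** In 20,000 simulated trials at 30% in both arms, McNemar rejects in 4.9% (3.5% with continuity correction). At 30% versus 15%, power is 75.5% (70.1% with correction), against 76.3% for Pearson.

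**The case against.** The best defence is that this is a slip of naming. The sample size section already specifies a suitable unpaired test, and a competent analyst would probably notice. That bears on how likely the harm is. It does not correct the sentence, which names McNemar for the primary outcome and three others. Nor can the point be left to an unseen SAP, because the article fixes the test rather than leaving it open.

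A second defence concerns size, and it partly stands. The 99.96% figure applies only if McNemar is run on the arm-by-outcome table, which the document does not say will be done. Under random pairing, type I error and power are close to Pearson's. The pairing example was also chosen near the threshold. At totals close to the design assumption, 33/109 versus 16/109 (Pearson p = 0.0058), every possible pairing gives p between 0.00004 and 0.015, so the decision at 0.05 would not change. These points limit the harm under the second reading to arbitrariness in near-threshold results. They do not make the test appropriate.

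A third remark is that a plain two-sample test ignores the stratification by centre, although the article expects laparoscopy and open-close rates to differ between centres. That is a reason to refine the replacement, not to retain McNemar.

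**Conclusion.** The concern holds. The named primary test does not fit the design and conflicts with the test on which the trial was powered. Read as the arm-by-outcome table, the primary p-value is invalid, with near-certain rejection under the null at a 30% event rate. Read as invented pairs, it is arbitrary: the same arm totals can fall on either side of 0.05, although the long-run error rate stays near 5% if the pairing is random. The same fault applies to the three secondary between-arm outcomes in that sentence. The figures assume 1:1 allocation and 109 evaluable patients per arm; the mismatch between test and design depends on neither. Because this fixes the trial's headline p-value, it must be corrected before analysis.

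**What to change.** In the Data analysis section, replace McNemar's test with a two-sample test for independent proportions, such as Pearson's chi-squared, in line with the sample size section. Do this for the primary outcome and for incomplete CRS-HIPEC, non-peritoneal findings before surgery, and early recurrence or residual disease. Report each risk difference with a 95% confidence interval. A Cochran–Mantel–Haenszel test or logistic regression accounting for centre would be a worthwhile refinement, since randomisation is stratified by centre, but the correction is sound without it. Keep McNemar only for comparisons of two assessments in the same patients.

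The cost is one sentence in the protocol and the corresponding SAP text. No new data are needed.

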### Data collection

Basic clinical information is collected, including patient history, primary tumor location, tumor histology, previous surgical procedures, chemotherapy and/or radiotherapy history, and serum biomarkers. For each abdominal assessment preformed to assess eligibility for CRS-HIPEC (CT, MRI, laparoscopy, and laparotomy), a case report form (CRF) is filled out including the same parameters for each assessment, where appropriate. These parameters include the PCI, the presence of organ infiltration, the presence and pattern of miliary spread, presence of non-PM (such as liver and lymph node metastases) and diaphragmatic involvement. Parameters specific to radiological assessments (CT, MRI) include scan quality, scan completion, presence of extra abdominal metastases (retroperitoneum, chest), and presence of pleural effusion. For each radiological finding, the reader will indicate whether the feature is present (yes/no) and how certain he or she is of that decision (not certain/ quite certain/ certain). Parameters specific to surgical assessment include extent of adhesiolysis and accessibility. Surgical findings are considered the reference standard. No confidence level will be applied to those parameters. For the laparotomies that proceed to CRS-HIPEC, a separate CRF registers which resections, excisions, and/or extirpations have been performed, as well as the completeness of cytoreduction (resection status). All data is collected by the local research team, consisting of at least one radiologist, one surgeon, and a research nurse and/or medical data manager. The pseudo-anonymized data is entered and stored with the same clinical trial management software used for randomization (ALEA clinical, Abcoude, The Netherlands) in an ISO 27001 certified hosting facility in the Netherlands.

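### Incomplete CRS-HIPEC is compared between arms without any baseline covariate although the CT form includes PCI; adjusting for it would be a cheap, modest gain

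*Protocol article*

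**What the plan says.** Under Eligibility criteria, patients enter only after CT has led to their being considered for CRS-HIPEC, so the scan precedes randomisation in everyone. Under Data collection, "For each abdominal assessment preformed to assess eligibility for CRS-HIPEC (CT, MRI, laparoscopy, and laparotomy), a case report form (CRF) is filled out", and "These parameters include the PCI, the presence of organ infiltration". The section adds that the parameters are the same for each assessment where appropriate. It does not say when the CT form is filled in relative to allocation.

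The Data analysis section names McNemar's chi-squared test for the between-arm difference in preventable explorations, "as well as the difference in incomplete CRS-HIPECs, non-peritoneal findings before surgery" and early recurrence or residual disease. No covariate or stratum is named, and CT-PCI enters none of the analyses described. Under Sample size calculation, by contrast, the trial was sized "With a two-sample two-sided test of binomial proportions and an α of 0.05". Blinding is stated to be impossible.

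**The concern.** Outcome measures lists incomplete CRS-HIPEC (R2a, R2b or open-close) as a secondary outcome. Whether complete resection is feasible depends largely on the extent of peritoneal disease, and PCI measures that extent. A CT reading of PCI from before randomisation is therefore a natural prognostic covariate, and the plan already collects it. A test without covariates leaves any such information unused.

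The stake is precision. Incomplete CRS-HIPEC may produce few events, so its risk difference will have a wide interval, and chance imbalance in disease extent between arms would add to the noise. Adjustment for a prognostic baseline value reduces both. The test has to be rewritten in any case, because McNemar's test needs matched pairs and the arms consist of different patients.

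**Working it through.** **Inputs from the article.** "expected reduction of futile surgical explorations from 30 to 15% by MRI staging"; two-sided α 0.05; β 0.20; "an expected drop-out rate of 20%, 272 patients are to be included in total". The allocation ratio is not stated; 1:1 is assumed.

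**The plan's own figure.** With pooled p = 0.225, n per arm = [1.96·√(2·0.225·0.775) + 0.842·√(0.30·0.70 + 0.15·0.85)]² / 0.15² = 120.5, so 121 per arm and 242 in total. Dividing by 0.8 for drop-out gives 303, so the stated 272 is not reproduced from the stated inputs. It matters here only because it sets the evaluable number: 272 × 0.8 = 217.6, or about 109 per arm. Power for the primary comparison is then 75.8%.

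**Formula for the gain.** If CT-PCI explains a share R² of the outcome variance, the variance of the adjusted risk difference is about (1 − R²) times the unadjusted one, and the standard error is multiplied by √(1 − R²). The article gives no R² and no correlation between CT-PCI and surgical PCI, so all values below are assumed.

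**Incomplete CRS-HIPEC.** Three sets of assumptions were tried.
- Large samples (about 400,000 patients), right-skewed PCI, CT underestimating it, CT-surgical correlation 0.59 to 0.92, incomplete CRS 11–12% in arm B and 4–5% in arm A: R² is 0.09–0.24 in arm B and 0.01–0.05 in arm A. The variance of the risk difference falls by about 7–19%.
- Large samples, one population without arms, PCI mean 12 and SD 8, correlation 0.3 to 0.9, incomplete CRS about 23%: R² is 0.03–0.29 with a linear term.
- Trial size (109 per arm), correlation 0.5 to 0.95, with and without truncating CT-PCI to mimic exclusion of patients with CT contraindications: the variance falls by about 0–11%. Some fits showed separation because events were few.

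The third set is closest to what the trial would deliver, because it carries the cost of fitting a model to few events. At 11.5% versus 4.5% and 109 per arm, expected events are 109 × 0.115 ≈ 12.5 and 109 × 0.045 ≈ 4.9, about 17 together. The unadjusted standard error is √[(0.115·0.885 + 0.045·0.955)/109] = 0.0364, a 95% half-width of 7.1 percentage points. With an 11% fall in variance it is 7.1 × √0.89 = 6.7 points. That equals 217.6/0.89 − 217.6 ≈ 27 extra evaluable patients at best, and none at the lower end.

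**Primary outcome.** It counts surgery at PCI above 24 and exploratory surgery at PCI below 15, so risk is not monotone in PCI. Large-sample results were a 1–11% variance reduction under the first set of assumptions. Under the second, R² was about zero with a linear term and 0.000–0.033 with a quadratic one. At trial size the change in variance was about −1% to 3%. An R² of 0.03 moves power from 75.8% to 77.1%; about 0.10 would be needed to reach 80%.

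**The case against.** An unadjusted comparison of randomised arms is valid, and the trial was sized on one. Covariates, functional form and imputation are commonly left to a statistical analysis plan, which is not shown. This stands against calling the missing adjustment an error. It does not remove the suggestion, because the article names a specific test for this outcome and that test has to be replaced anyway.

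A reader might infer that every patient has a CT-PCI recorded before randomisation. The documents do not support that. The scan comes before inclusion, but the timing of the form is not given, and PCI is recorded where appropriate. In an unblinded trial, a CT-PCI scored after the arm A MRI is known would not be a safe baseline covariate.

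A reader might also infer a large loss of precision across all between-arm tests. The Abstract and Background describe CT as underestimating tumour load and as falling short for total burden. Underestimation alone still lets CT rank patients, but imprecision lowers R², and excluding patients with CT contraindications may narrow the CT-PCI range. The assumed 11–12% incomplete rate in arm B is below the 20–40% that the Background and Discussion cite, so event counts could be higher than shown.

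Finally, incomplete CRS-HIPEC arises only in patients taken to surgery, and the staging arm helps decide who is. Among operated patients, CT-PCI adjustment would not remove that selection. Nor does the article call this outcome the main check on harm; it is one of seven secondary outcomes.

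**Conclusion.** The point holds as a modest efficiency gain confined to incomplete CRS-HIPEC. The comparison stated for it uses no baseline covariate, while a form that includes PCI exists for a CT done before inclusion. The expected benefit at trial size is about 0–11% of the variance of the risk difference, or at most about 6% of interval width. This rests on assumed PCI distributions, event rates and CT-surgical correlations; other assumptions give larger figures, and the documents cannot settle which apply. It also requires a CT-PCI reading that is independent of allocation. For the primary outcome the gain is close to nil, and adjustment should not be expected to make good the gap between 75.8% and 80% power. McNemar's test on independent arms is the more serious fault in the same sentence and must be corrected whether or not this suggestion is adopted.

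**What to change.** When McNemar's test is replaced by an independent-samples comparison, prespecify the following for incomplete CRS-HIPEC:
- Count events among all randomised patients, with those not operated on counted as having no incomplete procedure.
- Fit a logistic model with arm and one linear CT-PCI term. If events are sparse, use a penalised fit such as Firth's, with the intercept corrected before standardising, since the penalty pulls average fitted risks towards one half.
- Report the standardised (marginal) risk difference with its 95% interval.
- Score and lock the CT form before allocation is released, or have the CT scored by a reader who does not know the arm.
- State a simple imputation rule for missing CT-PCI.

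For the primary outcome CT-PCI adjustment is optional; if used, it needs a non-linear term.

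The cost is a change of analysis wording and one rule on the order of data entry. No new data are needed. The downside is a slightly less simple model and some imputation.
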